## Abstract

**Background:**

We investigate and try to find out the optimal duration and intensity for the treatment and content useful for clinical work. The aim of our study is to evaluate the effects of lifestyle intervention on the management of childhood overweight and to explore the factors that contribute to the outcome, as well as the costs for the health care system. The hypotheses of the study are that lifestyle intervention is efficient in reducing BMI-SDS and thus effective in preventing overweight from progressing to obesity, and it is also cost-effective.

**Methods and analyses:**

We aim to recruit 80 children and they randomize either to an intervention group or a control group with standard care. The intervention group receives intensive, family-based diet, and physical activity counseling, delivered by a multidisciplinary team of a pediatrician, a nurse, and a clinical nutritionist. The control group does not receive any lifestyle intervention during the study. The inclusion criteria are age of 6–12 years, weight-for-height ≥  + 40% or ≥  + 30%, and increasing curve. All participants fill out the study questionnaires and plasma samples are taken at baseline and at 12 months. Outcome variables will be compared between intervention and control groups.

**Discussion:**

If the effects of this lifestyle intervention are positive and it is also cost-effective, the implication of our study will be of great importance to the treatment of childhood obesity and to improve the health care system.

**Trial registration:**

ClinicalTrials.gov NCT06126679. Registered on 25 October 2028 in Finland.

ORCID: [name].

## Introduction

Obesity is the most prevalent chronic health condition in the pediatric population [1]. The number of school-aged children and adolescents with obesity has increased more than tenfold in just 40 years [2]. The costs of overweight and obesity have been increasing during the past decades and obesity has become a major global health challenge. An estimated 216 million children were overweight in 2016 [2]. In Finland, at least 25% of boys and almost 20% of girls aged 2–16 years are overweight, and 9% of boys and 4% of girls are obese [3]. If both parents are obese the child’s risk of being obese as an adult is 6- to 15-fold as compared with a child without obese parents [4, 5].

Being overweight in childhood is associated with an increased risk of obesity and many chronic diseases and other health problems such as mental and psychological issues in later life [6]. It is associated with an increased risk of hyperinsulinemia, insulin resistance, prediabetes, and subsequently type 2 diabetes in childhood. Mean arterial blood pressure increases significantly with increasing BMI in children [7]. Nonalcoholic fatty liver disease (NAFLD) is a chronic liver disease resulting from excessive fat accumulation in the liver and is strongly associated with obesity in children [8]. Obese or overweight children are also often affected by weight-related stigmatization, discrimination as well as frequent teasing by peers causing psychosocial health problems, such as low self-esteem, body dissatisfaction, eating disorders, depression, anxiety, and social isolation [9] and low health-related quality of life (HRQoL) [6, 9, 10]. The risks of health problems among overweight or obese children who become non-obese by adulthood are like those who were never obese [11].

There is also proportionality between BMI and costs for society [12]. The lifetime cost is almost three times greater per child with obesity than per child with overweight [12]. The costs of overweight and obesity in adulthood are greater the longer the person has been obese, especially if present from childhood or adolescence [12].

Clinical interventions to manage childhood obesity have the potential to reduce the prevalence of obesity in adults, improve long-term quality of life, and reduce health care costs [13, 14]. Lifestyle interventions in children, including multicomponent guiding with healthy diet, increasing physical activity, and decreasing sedentary time with behavioral change can be effective in achieving reductions in body mass index and can decrease the risk of health problems associated with obesity in adulthood [6, 15–17]. Weight loss is greater when the duration of treatment is longer than 6 months [17]. Estimated contact hours and number of sessions are the intervention components associated with effect size [18]. A meta-analysis indicates that lifestyle interventions incorporating a dietary component as a critical part of the treatment of childhood obesity led to significant weight loss [17].

Several trials have shown that pediatric obesity treatment is most effective when it starts at a younger age [6, 19, 20]. Good motivation for treatment and adherence to the protocol have contributed to a favorable outcome [20]. Lifestyle interventions are safe for children. They have few harms, and studies have found no evidence of adverse effects on growth, eating disorder pathology, or mental health [15, 21].

Further studies are needed to find out the optimal duration, intensity, and content, as well as the long-term effectiveness of dietary and physical activity interventions on overweight and obese children. There are only a few evaluations of the cost-effectiveness for the treatment of childhood overweight and obesity and more information on the cost-effectiveness of weight management interventions is needed.

We investigate the effectiveness and cost-effectiveness of a randomized 1-year dietary and physical activity intervention of childhood obesity (Hyvinkää Childhood Obesity Study, HCOS). This intervention model is in use in the treatment of children with obesity at Hyvinkää Hospital in Finland. The aim of our study is to investigate the effects of lifestyle intervention on the management of childhood overweight and the prevention of developing obesity. The second aim of our study is to study the cost-effectiveness of the intervention. The hypotheses of the study are that lifestyle intervention is efficient in reducing body mass index standard deviation score (BMI-SDS) and thus effective in preventing overweight from progressing to obesity, and it is also cost-effective. Our study will also provide more information about the lifestyle and quality of life of overweight or obese children. If we can stop excessive weight gain in childhood, we might be able to help overweight children feel better and live healthier and save society’s expenses.

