## Methods and analyses

### Participants

Hyvinkää Childhood Obesity Study, HCOS is a randomized controlled clinical trial. Study participants are recruited from the primary care and community settings within the Helsinki University Hospital (HUS), Hyvinkää hospital area in Southern Finland. In schools, public health nurse recommends children and their parents to participate in this study if the child meets the inclusion criteria. In addition, we use passive recruitment methods via local newspapers and social media, flyers, and posters at schools and other community venues.

The inclusion criteria for the study are overweight (weight for height at least + 40% or ≥ 30% and it is rising) and age of 6–12 years. Exclusion criteria are diagnosed endocrine diseases and mental illnesses. Participants must be well-motivated and participate in the study with one or both parents. Eligible participants are randomized to either the intervention group or the control group with standard care using opaque sealed envelopes.

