### Anthropometric measurements

Body height and weight are measured by specialist nurses, according to the methods generally used in Finland. Weight is measured in light underwear using a calibrated electronic scale with an accuracy of 0.1 kg as the mean of two measurements. Height is measured with an accuracy of 0.1 cm and the mean of the two measurements of barefoot height is used. ISO-BMI is calculated as weight (kg) divided by height (m) squared and BMI-SDS is computed using Finnish references [22].

Waist circumference is measured twice to an accuracy of 0.1 cm while standing and with an unstretchable measuring tape adjusted horizontally. Waist circumference is measured during expiration at mid-distance between the bottom of the rib cage and the top of the iliac crest.

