## Discussion

There are several previous lifestyle intervention studies, which have the potential to reduce BMI and decrease the risk of health problems associated with obesity [6, 15–17]. However, only seldom these are applicable in clinical work and there are only a few evaluations of the effectiveness with cost-effectiveness. This is why it will be of great importance to find out the optimal content, duration, and intensity of the treatment of overweight and obesity in children. Our study will provide new information on this.

Our study will provide new information about the effects and cost-effectiveness of lifestyle intervention in overweight or obese children in Finland. If the effects of the lifestyle intervention are positive and it is also cost-effective, the implication of our study will be of great importance to the treatment of childhood obesity, health care providers, and overweight or obese individuals.

The results of the present study will provide more information about the lifestyle and quality of life of overweight or obese children in Finland. If we can stop excessive weight gain in childhood, we might be able to help overweight children feel better and live healthier. Being overweight in childhood is associated with an increased risk of obesity and increased risk of many diseases and other discomforts such as mental and psychological issues [6]. Due to the high number of overweight or obese children, it will be challenging to take care of all the complications associated with obesity. However, the risk of health problems among overweight or obese children who become nonobese by adulthood is like those among persons who were never obese [11]. The lifetime cost is greater per child with obesity than per child with overweight and costs are greater the longer the person has been obese [12]. Because of these reasons, it is very important to try to stop excessive weight gain in childhood. If our lifestyle intervention is efficient in reducing BMI-SDS and cost-effective, the treatment model can be taken into wider use, and we can save society’s expenses.

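### A lower mean BMI-SDS would not by itself show that overweight was kept from progressing to obesity, yet the hypothesis infers one from the other

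*Protocol article*

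**What the plan says.** The Introduction of the protocol article states the aim as "the management of childhood overweight and the prevention of developing obesity". The hypothesis, which also appears in the Abstract, is that the intervention lowers BMI-SDS and is "thus effective in preventing overweight from progressing to obesity".

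The rest of the article fixes the following:

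- **Sample size** (Calculation of the sample size): 40 children per group, based on a difference of 0.4 in the change of BMI-SDS, two-sided 0.05, 80% power and 10% dropout.
- **Effectiveness analysis** (Statistical analyses): a general linear model for repeated measures, which compares means.
- **Eligibility** (Participants): "overweight (weight for height at least + 40% or ≥ 30% and it is rising) and age of 6–12 years". On exclusions: "Exclusion criteria are diagnosed endocrine diseases and mental illnesses". There is no upper weight limit.
- **Population as described elsewhere**: the Introduction expects information on the "lifestyle and quality of life of overweight or obese children", and the Discussion speaks of "lifestyle intervention in overweight or obese children in Finland".
- **Indices** (Anthropometric measurements): "ISO-BMI is calculated as weight (kg) divided by height (m) squared". BMI-SDS is computed separately from Finnish references.

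The article gives no obesity threshold and no progression outcome.

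**The concern.** Progression to obesity is an event in a child who is not yet obese: the child crosses a threshold during follow-up. A difference in mean BMI-SDS across all randomised children is a different quantity. It averages children who could cross the threshold with any who are already above it, and it does not say where on the scale the change occurred. Even among children below the threshold, a shift in the mean prevents progression only in those who would otherwise have crossed.

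This matters because prevention of obesity is part of the stated aim and carries some of the economic argument. The Introduction says that lifetime cost is almost three times greater per child with obesity than per child with overweight. A reader who accepts the inference could credit the trial with moving children across that boundary when only a mean had been compared.

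**Working it through.** **1. What the trial is sized for.** Inputs from Calculation of the sample size: difference 0.4, two-sided 0.05, power 80%, dropout 10%. The SD of the change is not stated, so the published figure cannot be reproduced from stated inputs alone. Reading 0.4 as BMI-SDS units and assuming SD 0.6:

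n = 2 × (1.960 + 0.842)² × 0.6² / 0.4² = 35.3, rounded up to 36 per group; 36 / 0.90 = 40.

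This matches the stated 40. The section also words the difference as 0.4 SD. Read as a standardised difference, that gives 2 × (1.960 + 0.842)² / 0.4² = 98.1, rounded up to 99, and 99 / 0.90 = 110 per group. That ambiguity is a separate matter. Under either reading the design is sized for a difference in means.

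**2. Whether a mean difference of 0.4 can arise with no progression prevented.** Let f be the share already obese at baseline, taken as equal in both groups, and suppose there is no effect in the others. The difference needed in the obese children is 0.4 / f.

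| Share already obese (assumed) | Difference needed in them | Overall difference |
|---|---|---|
| 25% | 0.4 / 0.25 = 1.60 | 0.4 |
| 50% | 0.4 / 0.50 = 0.80 | 0.4 |
| 75% | 0.4 / 0.75 = 0.53 | 0.4 |

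The larger the share already obese, the smaller the effect needed in them alone. This shows that the inference can fail. It does not predict that it will.

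**3. What a direct comparison of progression could show.** The article gives no progression rate and no share already obese, so both are assumed. Completers: 40 × 0.90 = 36 per arm. The effect is a halving of the control rate. Power is from the two-sided normal approximation with pooled variance under the null.

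| Control vs intervention | 36 at risk per arm (none obese at entry) | 18 per arm (half obese) | 9 per arm (three quarters obese) | At-risk completers per arm for 80% power |
|---|---|---|---|---|
| 20% vs 10% | 22% | 13% | 8% | 199 |
| 30% vs 15% | 33% | 19% | 11% | 121 |
| 40% vs 20% | 46% | 25% | 15% | 82 |
| 50% vs 25% | 59% | 34% | 19% | 58 |

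For precision, take 40% vs 20%. The standard error of the difference is √[(0.40 × 0.60 + 0.20 × 0.80) / n]. With n = 36 it is √(0.40 / 36) = 0.105, so the 95% CI half-width is 1.96 × 0.105 = 0.21. With n = 18 it is √(0.40 / 18) = 0.149, half-width 0.29. Around a difference of 20 percentage points, both intervals include zero.

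**The case against.** The strongest reply is that prevention is worded as an expected consequence of lower BMI-SDS, not as a separately tested hypothesis. The Discussion makes wider use of the model depend on reducing BMI-SDS and on cost-effectiveness, not on prevention of obesity. A categorical secondary outcome is also something an article may leave to the full protocol or the analysis plan. This part stands: the absence of such an analysis here is not a fault, and nowhere does the article say that progression will be declared prevented. What the reply does not rescue is the stated inference, which an unseen document could supplement but not make valid.

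Three stronger readings are tempting and are not supported.

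- **A known or large share of the children are obese at entry.** Participants calls the entrants overweight: "The inclusion criteria for the study are overweight". No obesity threshold is given. The descriptions in the Introduction and Discussion show that obese children are eligible and expected, but not how many.
- **The ISO-BMI formula will misclassify most children.** The term occurs once. It is not used for eligibility, sample size, hypothesis or classification. The documents give neither an adult-equivalent meaning nor a cut-off for it, and any count of misclassified children would rest on assumed median weights and would change with height and degree of overweight.
- **The BMI-SDS result is undermined.** It is not, because BMI-SDS has its own reference.

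**Conclusion.** The point holds as a limit on what may be concluded. The aim and hypothesis include prevention of obesity, the stated sample size and analysis address mean BMI-SDS, and the population is not restricted to children who could still progress. A significant mean difference would support the BMI-SDS hypothesis and would leave the progression claim open.

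The textual mismatch needs no assumption. Its practical size depends on the unstated share of children already obese. At an assumed 50%, an effect of 0.8 confined to them reproduces the planned 0.4. The power figures of 22% to 59% with none obese at entry, and 13% to 34% with half, rest on assumed control rates of 20% to 50%, a halving of progression and 36 completers per arm.

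A minor point goes with this. The formula given for ISO-BMI is plain weight over height squared, with no age or sex adjustment. It should not be used to classify obesity in children aged 6 to 12.

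**What to change.** Choose one of two changes.

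1. **Restrict the claim.** Word the hypothesis and all conclusions in terms of BMI-SDS, and drop the inference to prevention of obesity. This costs only wording.
2. **Add one exploratory secondary analysis.** Before the outcome data are examined, name an age- and sex-specific obesity threshold from the Finnish reference already used for BMI-SDS. Among children below it at baseline, compare the proportions above it at 12 months, reported as a difference with 95% CI and labelled exploratory. Report how many children in each group were already above the threshold at baseline.

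The second option uses height and weight already collected at both visits. Its cost is an imprecise estimate, because the at-risk subset is at most about 36 completers per arm. It also inherits the limitation admitted under Strengths and limitations, that the two groups are measured by different staff in different places, since a threshold is applied to those measurements at both visits.

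With either option, correct the sentence under Anthropometric measurements so that the weight-over-height-squared formula is labelled BMI. If ISO-BMI is to be used at all, state how it is derived.

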## Methods and analyses

### Participants

Hyvinkää Childhood Obesity Study, HCOS is a randomized controlled clinical trial. Study participants are recruited from the primary care and community settings within the Helsinki University Hospital (HUS), Hyvinkää hospital area in Southern Finland. In schools, public health nurse recommends children and their parents to participate in this study if the child meets the inclusion criteria. In addition, we use passive recruitment methods via local newspapers and social media, flyers, and posters at schools and other community venues.

The inclusion criteria for the study are overweight (weight for height at least + 40% or ≥ 30% and it is rising) and age of 6–12 years. Exclusion criteria are diagnosed endocrine diseases and mental illnesses. Participants must be well-motivated and participate in the study with one or both parents. Eligible participants are randomized to either the intervention group or the control group with standard care using opaque sealed envelopes.

#### Calculation of the sample size

Power calculation was performed based on the assumption that there would be a difference of 0.4 in the change of body mass index standard deviation score (BMI-SDS) between the intervention and the control groups. Calculations on a difference of 0.4 SD in the change of BMI-SDS, at the level of statistical significance of 0.05 based on two-sided testing and with power of 80% and the assumption that 10% of participants will drop out in both groups the estimated sample size was 40 children per group.

Thus, we aim to recruit 80 children, targeting 40 children in the intervention group and 40 children in the control group.

## Methods

### Study visits

All participants fill out the study questionnaires and nurses measure height, weight, waist circumference, and blood pressure at baseline and at 12 months (Table 1). Participants in the intervention group have five visits to the hospital (at baseline and 3, 6, 9, and 12 months after baseline) including a total of 10 contact hours. Participants in the control group continue with the standard care in primary care. In the intervention group, all measurements of the participants are performed in the hospital. In the control group, measurements are performed in primary care. the same measurements were used in both groups. Costs in both groups will be documented. Further follow-up is possible to collect from health inspections of school health care.

**Table 1 Tab1:** SPIRIT figure of content for the schedule of enrolment, interventions, and assessments

	**Study period**							
	**Enrolment**	**Allocation**	**Post-allocation**					**Close-out**
**Timepoint**^**b**^	*** − t***_**1**_	**0**	***t***_**1**_	***t***_**2**_	***t***_**3**_	***t***_**4**_	***t***_**5**_	***t***_**6**_
**Enrolment:**								
** Eligibility screen**	x							
** Informed consent**	x							
** Allocation**		x						
**Interventions:**								
*** Intervention group***			x	x	x	x	x	
*** Control group***			x				x	
**Assessments:**								
*** Anthropometric measurements***			x		X^a^		x	
*** Blood pressure***			x		X^a^		x	
*** Laboratory values***			x				x	
*** Study questionnaires***			x				x	
*** Costs of the treatment***								x

^a^Only intervention group

^b^− *t*_1_ = recruitment, *t*_1_ = baseline, *t*_2_ = 3 months, *t*_3_ = 6 months, *t*_4_ = 9 months, *t*_5_ = 12 months, *t*_6_ = after the intervention period

### Anthropometric measurements

Body height and weight are measured by specialist nurses, according to the methods generally used in Finland. Weight is measured in light underwear using a calibrated electronic scale with an accuracy of 0.1 kg as the mean of two measurements. Height is measured with an accuracy of 0.1 cm and the mean of the two measurements of barefoot height is used. ISO-BMI is calculated as weight (kg) divided by height (m) squared and BMI-SDS is computed using Finnish references [22].

Waist circumference is measured twice to an accuracy of 0.1 cm while standing and with an unstretchable measuring tape adjusted horizontally. Waist circumference is measured during expiration at mid-distance between the bottom of the rib cage and the top of the iliac crest.

### Blood pressure

Blood pressure is measured manually by a calibrated meter. The measurement protocol includes, after a 5-min rest, three measurements from the right arm in the sitting position at 2-min intervals. The mean of all three measurements is used as the systolic and diastolic blood pressures.

### Laboratory analyses

Plasma samples are taken after 12-h fasting at baseline and at 12 months (Table 1), and they are performed in the laboratory of HUS in Finland. Laboratory analyses include blood count (hemoglobin, hematocrit, total red cell count, total white cell count, and thrombocytes), plasma concentrations of total cholesterol, high-density lipoprotein (HDL) cholesterol, low-density lipoprotein (LDL) cholesterol, triglycerides, glucose, alanine transaminase (ALAT) and high-sensitivity C-reactive protein (hs-CRP), and serum concentrations of insulin, thyroxine and thyroid-stimulating hormone (TSH), and glycosylated hemoglobin (HbA1c).

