### Statistical analyses

The statistical analyses will be performed using the SPSS statistical analysis software (IBM Corporation, Armonk, NY). Baseline characteristics will be compared between the intervention and the control groups using independent samples *T* test. Changes within the intervention and the control groups during the 1-year study period will be tested using paired samples *T* test and the effectiveness of the intervention will be investigated using a general linear model for repeated measures.

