## Trial status

The Hyvinkää Childhood Obesity Study (§142/2018, HUS/2666/2018) is conducted in coordination with HUS Hyvinkää hospital and community settings within the Hyvinkää area and started on 18 December 2018. The first participants started the intervention in January 2019. In early 2020, the COVID-19 pandemic started in Finland, and because of that, the recruitment of participants slowed down and was partially interrupted. The last visits of participants will be at the end of 2023 or at the latest at the beginning of 2024, and after these, the last study questionnaires will be returned. In the future, the study material will be supplemented with follow-up measurements in school health care. Because of the interruption of the COVID pandemic, the study has been delayed and this protocol article is only submitted now.

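### One set of mean-based tests of change, with no scale or baseline covariate stated, suits the skewed laboratory variables poorly and costs those comparisons power if applied to measured values

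*Protocol article*

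**What the plan says.** Protocol article, Laboratory analyses: "Plasma samples are taken after 12-h fasting at baseline and at 12 months (Table 1"). The panel is broad and includes "alanine transaminase (ALAT) and high-sensitivity C-reactive protein (hs-CRP), and serum concentrations of insulin", as well as triglycerides. Table 1 shows laboratory values at baseline and 12 months only, so each variable has two time points.

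Protocol article, Statistical analyses: "Changes within the intervention and the control groups during the 1-year study period will be tested using paired samples" t tests, and "the effectiveness of the intervention will be investigated using a general linear model for repeated measures". No outcome is treated differently from another. The section states neither measured nor transformed values, and no baseline covariate. Under Strengths and limitations, age and body height are mentioned as possible adjustments in place of puberty staging; the baseline value of the outcome is not.

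The Introduction's hypothesis is that "lifestyle intervention is efficient in reducing body mass index standard deviation score (BMI-SDS"), and that the intervention is cost-effective. The sample size calculation also concerns BMI-SDS. No hypothesis is stated for hs-CRP or any other laboratory variable.

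**The concern.** BMI-SDS is already a standardised score, so tests on means suit it reasonably well. hs-CRP is strongly right-skewed, and insulin, triglycerides and ALAT are skewed to a lesser degree. With two time points, the group-by-time test of a repeated-measures general linear model is the same as a two-sample t test on change. On measured values, the variance of that change comes mostly from the few children with high results. An acute infection at either visit adds such results for hs-CRP. The comparison between arms then has little power, even where the typical child's value has fallen substantially.

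At stake is how informative the laboratory comparisons are. Choosing a transformation or dropping outliers after seeing the data would be data-driven, so the scale should be settled beforehand.

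**Working it through.** **Inputs from the article.** 40 children per group and 10% dropout give 40 × 0.9 = 36 completers per arm; testing is two-sided at 5%. The plan has no figure for any laboratory variable to reproduce. Its 40 per group is for BMI-SDS: a difference of 0.4 units with an SD of about 0.6 (not stated) needs 36 evaluable, and 36 / 0.9 = 40. That figure is used here only for the number of completers.

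**Assumed inputs (none is in the documents).** hs-CRP log-normal, median 1.5 mg/L, log-SD 1.1, correlation 0.6 between visits on the log scale. An infection multiplies a value by 10 and affects 0, 5 or 10% of samples. The true effect is a halving.

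**Closed form, no infections, log scale.**
- Effect: −ln(0.5) = 0.693.
- SD of log change: 1.1 × √(2 × (1 − 0.6)) = 0.984. SE = 0.984 × √(2/36) = 0.232. Ratio 0.693 / 0.232 = 2.99. Power ≈ Φ(2.99 − 1.96) = 85%.
- Residual SD with log baseline as covariate: 1.1 × √(1 − 0.6²) = 0.88. SE = 0.88 × √(2/36) = 0.207. Ratio 0.693 / 0.207 = 3.34. Power ≈ Φ(3.34 − 1.96) = 92%.

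**Raw scale, no infections.**
- Mean: 1.5 × exp(1.1²/2) = 2.75 mg/L, so a halving removes 1.37 mg/L.
- SD of change without an effect: 2.75 × √(2 × (e^1.21 − e^0.726)) = 4.4 mg/L.
- The effect is therefore about 1.37 / 4.4 = 0.31 SD, against 0.693 / 0.88 = 0.79 SD on the adjusted log scale. The normal formula is unreliable for such skewed changes, so raw-scale power is taken from simulation.

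**Simulated power, true halving**

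| Samples infected | Raw change | Log change | Log, baseline-adjusted |
|---|---|---|---|
| 0% | 38% | 85% | 92% |
| 5% | 14% | 66% | 79% |
| 10% | 10% | 56% | 69% |

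The closed form matches the two log columns in the first row. Most of the gain comes from the scale: with no infections, 85 − 38 = 47 points from the log and 92 − 85 = 7 from the baseline covariate.

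**Smaller effect.** For a 30% fall with no infections, power is about 14% raw and 38% for the adjusted log analysis. Check: −ln(0.7) = 0.357; 0.357 / 0.207 = 1.72; Φ(1.72 − 1.96) ≈ 40%.

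**No effect.** The raw test rejects in about 3–4% of simulated trials, so type I error is not inflated.

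**A different infection model.** Here the log-SD is 1.0, an infection adds a median of 15 mg/L and the true fall is 40%. Power for raw change against log change is 33% against 67% with no infections, and 10% against 40% with 5% infected per visit. The four most extreme of 72 children carry about 63% of the raw sum of squares with no infection and about 74% with 5% infected. Skewness alone therefore causes much of the loss.

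**Excluding values above 10 mg/L.** In the multiplicative model this slightly lowers the power of the adjusted log analysis: one run gave 91/77/70% without exclusion and 88/75/64% with it, at 0/5/10% infected. In the additive model at 5% infected it raises the power of log change from 40% to 55%. Its value depends on inputs nobody has, so it belongs in a sensitivity analysis.

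**Insulin.** With assumed log-SD 0.5, correlation 0.6 and a true 20% fall, power is about 42% raw and 62% on the adjusted log scale.

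**The case against.** The strongest objection is that the article is silent on scale. A general linear model can be fitted to logged values, and transformations and outlier rules are commonly left to a statistical analysis plan or the full protocol, which the Data Availability section says can be obtained on request. This stands in part. A reader might infer that the plan fixes hs-CRP to be analysed as raw change; the text does not say so. The point survives because the article does choose the methods. It names one mean-based set without distinguishing outcomes, and a better one is available at almost no cost.

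Several stronger readings are tempting but unsupported:

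- **That the lack of a rule for acute illness at the draw is a defect.** Fasting is the only sampling condition given, and "Exclusion criteria are diagnosed endocrine diseases and mental illnesses". But postponing or repeating a sample is conduct normally left to the full protocol or a laboratory manual. With last visits due by early 2024, it is also largely too late.
- **That a few infected children decide the result.** Only the hs-CRP comparison is exposed, and raw power is poor even with no infections. One infection value of 15–40 mg/L would not outweigh a halving in the other 35 children of an arm: 35 × 1.37 = 48 mg/L.
- **That the pandemic made infected samples common.** The Trial status section says "In early 2020, the COVID-19 pandemic started in Finland" and that recruitment slowed. Strengths and limitations describes home schooling and fewer social contacts. Neither gives an infection rate on sampling days.
- **That a null result would be read as no anti-inflammatory effect.** The article makes no claim about inflammation.
- **That a real reduction would be missed under the plan and found under the fix.** The fix raises power, but for a 30% fall it remains low.

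**Conclusion.** The point holds as a minor improvement to the analysis. If the stated methods are applied to measured values, the comparisons of hs-CRP, and to a lesser degree insulin, lose much power. Triglycerides and ALAT share the skewness but were not simulated. For a true halving of hs-CRP the loss is from about 92% to 38% with no infections, and from about 79% to 14% with 5% of samples infected. These sizes rest wholly on the assumed distribution, correlation, infection model and effect. The direction does not depend on infections, and it was the same under a second infection model with a smaller effect. Type I error is not inflated, and the BMI-SDS hypothesis and its sample size are untouched.

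**What to change.** In Statistical analyses, state before any comparison between arms is seen that hs-CRP, insulin, triglycerides and ALAT at 12 months will be compared on the natural-log scale, with the log baseline value as covariate, and reported as ratios of geometric means with confidence intervals. Add one sensitivity analysis for hs-CRP that leaves out children with a value above 10 mg/L at either visit, applied identically and blind to arm. Both can be done on samples already drawn.

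Cost: a sentence or two of analysis wording. Results will be read as ratios rather than differences in mg/L, and a few children leave the sensitivity analysis.
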